**Figure 1 fig1:**
[figure not shown]
Flowchart of the study.

The Women’s Hospital at Zhejiang University School of Medicine is designated as the primary coordinating center, tasked with overseeing the comprehensive study design, implementation, quality control, and data management. The research initiative will be spearheaded by a Principal Investigator (PI) who possesses specialized expertise in breast cancer research and clinical management. The PI will be responsible for the daily operations of the study, including participant recruitment, data collection, and quality assurance. Consistent with standard oncology practice in China, all patients receive comprehensive care managed by a multidisciplinary team (MDT). Following MDT consensus, our core research team consist of specialists from various clinical disciplines integral to the management of breast cancer, such as: breast surgeons with proficiency in oncologic surgery and systemic therapy, pathologists skilled in breast cancer diagnosis and molecular characterization, diagnostic radiologists with specialization in breast imaging, and gynecologists equipped to address the unique hormonal considerations in premenopausal patients, and so on.

All participants were mandated to provide written informed consent, comprehensively outlining the study’s objectives, procedures, potential risks, and benefits, thereby ensuring participants’ full comprehension of the study content and voluntary participation. For ancillary studies involving the collection of biological samples and genetic testing, distinct informed consent forms were developed to further protect participants’ rights to information and autonomous decision-making. The study protocol received approval from the Research.

Ethics Board of Women’s Hospital, Zhejiang University School of Medicine (IRB-20250423-R) and was conducted in strict adherence to the Declaration of Helsinki and pertinent national regulations. An independent safety monitoring committee was established to ensure adequate protection of subject safety and legal rights. In addition, a research quality and data quality monitoring committee, jointly established by the hospital’s ethics committee, medical affairs department, research department, and data management center, reviews our raw data every quarter to ensure the smooth progress of this study.

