### Cohort classification

This study employed an observational prospective cohort design with non-randomized grouping based on real-world clinical practice. Patients were categorized into two groups according to the endocrine therapy regimen prescribed by their treating clinicians, taking into account individual disease characteristics, age, prior treatment history, and personalized clinical needs. The prescription of OFS + AI versus OFS + TAM is determined by the treating oncologist in accordance NCCN (3) based on clinicopathological risk factors. In brief: (1) OFS + AI is preferred for patients at high risk of recurrenceor those with contraindications to tamoxifen; (2) OFS + TAM is considered for patients with intermediate risk or those who cannot tolerate AI; (3) Patient preference and comorbidities (e.g., baseline cardiovascular risk, endometrial abnormalities) are taken into account. Any patient using oral contraceptives or levonorgestrel-releasing IUDs is required to discontinue/remove them prior to enrollment, since hormone receptor-positive breast cancer is a contraindication for systemic or local hormonal contraceptives.

To assess and address potential confounding, comprehensive baseline data were collected, including demographic characteristics (age, BMI, educational level, marital status), clinicopathological features (tumor size, lymph node status, TNM stage, histological grade), immunohistochemical markers (ER, PR, HER2 expression status, Ki-67 index), treatment-related factors (surgical approach, chemotherapy history, radiotherapy history), and laboratory parameters (estrogen levels). Patients who received (neo) adjuvant chemotherapy are eligible for inclusion. By strictly enforcing the hormonal inclusion criteria (FSH < 40 IU/L and Estradiol >20 pg./mL), we ensure that even patients with prior chemotherapy exposure are in a biochemically confirmed premenopausal state at baseline. For these patients, baseline sampling and assessment are performed at least 4 weeks after the last chemotherapy dose and prior to the initiation of endocrinotherapy. Chemotherapy history (regimen, number of cycles, dates) is recorded as a potential confounder, and subgroup analyses stratified by chemotherapy exposure will be performed.

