### Secondary outcomes

Prior to inclusion (at baseline), all patients undergo a systematic evaluation of GSM symptoms using standardized questionnaires, and only patients who report no GSM symptoms are eligible for inclusion. The clinical functional indicators comprised the Vaginal Health Index (VHI), Visual Analog Scale (VAS) scores for GSM, and International Consultation on Incontinence Questionnaire (ICIQ) scores for urinary symptoms. The VHI evaluated five dimensions through gynecological examination: vaginal discharge, pH value, epithelial integrity, moisture, and elasticity, with a cumulative score ranging from 5 to 25 points. Two attending gynecologists from our core multidisciplinary research team, each with over 10 years of clinical experience specializing in gynecological oncology and reproductive endocrinology, independently assessed the scores after undergoing protocol-specific standardized training to minimize inter-observer variability. The scores were then averaged, with measurements taken at time points baseline, 3 months, 6 months, and 12 months. GSM symptoms were assessed using a 10-cm VAS to independently evaluate subjective symptoms such as vaginal dryness, dyspareunia, and burning sensation, with scores ranging from 0 to 10 (0 indicating no symptoms and 10 indicating the most severe symptoms), completed by patients at each time point from baseline to 12 months. Urinary symptoms were evaluated using the International Consultation on Incontinence Questionnaire-Short Form (ICIQ-SF), with scores ranging from 0 to 21 points, measured at baseline, 3 months, 6 months, and 12 months, to encompass the full spectrum of genitourinary syndrome manifestations. Patients independently completed symptom questionnaires under the on-site guidance of research assistants, and comprehensive documentation of medication adherence, lifestyle changes, and other relevant factors potentially influencing vaginal microecology was maintained at each follow-up visit. The results are systematically documented in the electronic Case Report Form for all participants.

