## Discussion

This study protocol aims to address the knowledge gap in the existing literature regarding vaginal microbiota changes under pharmacologically induced hypoestrogenism. Most prior studies have focused on natural menopause populations and their associations between vaginal microbiota and GSM symptoms, such as cross-sectional analyses showing increased microbial diversity and significant Lactobacillus reduction in postmenopausal women, correlated with GSM (14, 15), or multicenter analyses confirming that non-Lactobacillus-dominant states increase GSM risk (16). However, longitudinal studies on endocrine therapy-induced “chemical menopause” in breast cancer patients are scarce; limited existing research, such as a 2024 cross-sectional analysis of postmenopausal breast cancer survivors showing increased vaginal abundance of Sneathia and Gardnerella in symptomatic patients, is constrained by small sample size and inability to infer causality (21); another 2021 Kazakhstan study observed Lactobacillus depletion in breast cancer patients but did not investigate relations to treatment or GSM (22). Through a prospective cohort design, this protocol adds to the emerging literature by systematically investigating the dynamic vaginal microbiota changes in premenopausal hormone receptor-positive breast cancer patients receiving OFS + AI or OFS + TAM therapy. Our study uniquely incorporates a direct comparison between OFS + AI and OFS + TAM regimens, a detailed dose–response analysis of microbiome shifts with GSM severity, and a comprehensive assessment of clinical functional outcomes including VHI, VAS, and urinary symptoms. We hypothesize that OFS + AI therapy will lead to more significant Lactobacillus reduction, increased microbial diversity, and exacerbated GSM symptoms, while OFS + TAM may offer protective effects due to its partial estrogenic activity (5, 8), thereby providing a scientific basis for personalized preventive strategies.

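### The VHI rating procedure lists training, independent scoring and averaging but not masking to regimen, so the secondary VHI comparison of OFS + AI with OFS + TAM is open to a rater expectation that averaging cannot remove

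*Protocol article*

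**What the plan says.** The Secondary outcomes section sets out the VHI procedure in some detail.

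- **Raters:** "Two attending gynecologists from our core multidisciplinary research team, each with over 10 years of clinical experience".
- **Items:** "vaginal discharge, pH value, epithelial integrity, moisture, and elasticity, with a cumulative score ranging from 5 to 25 points".
- **Safeguards:** the raters "independently assessed the scores after undergoing protocol-specific standardized training to minimize inter-observer variability".
- **Combination and timing:** "The scores were then averaged, with measurements taken at time points baseline, 3 months, 6 months, and 12 months".

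Cohort classification describes open allocation: "This study employed an observational prospective cohort design with non-randomized grouping based on real-world clinical practice", with the regimen chosen by the treating clinician. In the Study design section, the text after Figure 1 lists among the core team's disciplines "gynecologists equipped to address the unique hormonal considerations in premenopausal patients". The Discussion gives a directional expectation: "We hypothesize that OFS + AI therapy will lead to more significant Lactobacillus reduction, increased microbial diversity, and exacerbated GSM symptoms", with a possible protective effect of OFS + TAM. The Introduction's aims count the VHI among the measures of GSM severity.

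Table 1 schedules the VHI at baseline and 3, 6 and 12 months. It lists a separate vaginal pH measurement at the same four visits, and regimen, dosage and compliance at every visit. No part of the article mentions masking or blinding of any assessor.

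**The concern.** The listed safeguards answer one question, whether two examiners agree. They do not answer another, whether both examiners lean the same way when they know, or can guess, which drug the woman takes. In an open cohort whose team has written down which regimen it expects to do worse, the second question matters more for the regimen comparison.

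Comparing the regimens is a stated aim. The VAS and ICIQ-SF are completed by women on open treatment. The VHI is the only composite clinical outcome scored by an examiner, so it is where masking is practicable and where the study could obtain a reading less dependent on the patient's knowledge of her drug. If the raters share the expectation, a VHI difference in the predicted direction would look like confirmation of the VAS without being independent of that expectation. The analyses linking the microbiome to GSM severity through the VHI would carry the same error.

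**Working it through.** **1. What the safeguards can and cannot do.** Write rater j's score for a woman as T + b + e_j, where T is her true score, b an error both raters share and e_j rater j's own random error. The average is T + b + (e_1 + e_2)/2. If the random errors are independent with equal variance, averaging halves that variance. The term b is unchanged. Training and independent scoring act on e_j; neither withholds the regimen from the rater.

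**2. How much of the score is exposed.** Of the five items, pH is a reading. Discharge, epithelial integrity, moisture and elasticity, four of the five, depend on the examiner's judgement.

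**3. Whether later steps repair it.** Inverse probability weighting (Cohort classification) and propensity score matching (Statistical analysis) balance baseline covariates; they do not correct how an outcome is measured. Baseline VHI is taken before endocrine therapy starts, so adjusting for it cannot remove a rating difference that begins at month 3. Such a difference would enter the group and group-by-time terms of the planned mixed model.

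**4. Sensitivity of the comparison.** The plan states no VHI SD, expected difference or power, so there is no VHI figure to reproduce.

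Inputs from the article: 55 women per group (Sample size) and two-sided α = 0.05 (Statistical analysis). Assumptions: SD of the averaged VHI 3 or 4 points; true regimen difference 0; a shared rating error that separates the groups by b = 0.5 or 1 point. One point equals 0.25 on each of the four judged items.

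Formulas: SE = SD × √(2/55). The rejection rate is the probability that a two-sample t statistic with 108 degrees of freedom and noncentrality b/SE falls outside ±1.982.

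- SD 4: SE = 4 × √(2/55) = 0.763
- SD 3: SE = 3 × √(2/55) = 0.572

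| SD | b | b/SE | Rejection rate, no true difference |
|---|---|---|---|
| 3 or 4 | 0 | 0 | 5% |
| 4 | 0.5 | 0.66 | 10% |
| 3 | 0.5 | 0.87 | 14% |
| 4 | 1 | 1.31 | 25.5% |
| 3 | 1 | 1.75 | 41% |

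With 49 per group (the abstract's 10% attrition: 55 × 0.9 = 49.5), b = 1 gives 23% (SD 4) to 37% (SD 3). A smaller shift, b = 0.25, at 55 per group gives 6–7%.

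These figures describe one cross-sectional test, not the planned mixed model. They show how sensitive the comparison is to a shared shift, not how likely such a shift is.

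**The case against.** **The article is silent; it does not say the raters are unmasked.** It condenses a fuller protocol, and rater procedures could sit there. This stands as a limit on the wording. It does not remove the point, because the article does list the rating safeguards and their purpose, and all of them concern inter-observer variability.

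**The raters need not be treating clinicians.** A reader might infer from the core-team description that the two gynecologists manage these women. The text names disciplines involved in breast cancer care and gynecologists suited to hormonal questions; it does not say that the two VHI raters treat participants, and Cohort classification leaves prescribing to the treating oncologist. The inference is not supported.

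**Table 1 does not show that raters see the regimen.** Recording regimen and VHI at the same visit does not mean the examiner reads the entry. Data collection and management assigns data entry to research coordinators and makes eCRF access role-based. This stands.

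**The figures rest on assumptions.** Any assumed bias pushes rejection above 5%. The article also plans a Bonferroni correction where appropriate: at an illustrative threshold of 0.01 (0.05/5 outcomes), the 1-point shift gives about 10–20%, against a nominal 1%. This stands, so the figures serve only as illustration.

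**Scope is limited.** The VHI is secondary, the primary outcomes come from sequencing, and the written hypothesis names GSM symptoms rather than the VHI. The first two stand. The third has little force, since the Introduction uses the VHI to measure GSM severity. The separate pH measurement also offers a less subjective check that is already scheduled.

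**Conclusion.** The point holds as a correctable weakness in a secondary outcome. The plan's safeguards reduce random disagreement between the two raters and leave a shared expectation untouched; four of the five items are open to it, and no planned adjustment removes it. The regimen comparison on the VHI, and associations that use the VHI, are affected. Simpson diversity and Lactobacillus abundance are not rated by these examiners.

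The size is conditional: about 10–41% false positives instead of 5% for a shared shift of 0.5–1 point, given an assumed SD of 3–4 points, 55 per group and a single t-test at 5%. The article supplies neither the SD nor the shift.

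A reader might go further and conclude that the raters are unmasked, that bias will occur, or that the VHI cannot corroborate the VAS. The article supports none of these. If masking is already intended, one sentence settles the matter.

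**What to change.** Add to the Secondary outcomes section that the same two gynecologists score the VHI without access to the regimen, the VAS or ICIQ-SF answers, earlier VHI scores or sequencing results. They use a form carrying only the study number and visit; the coordinator records regimen and compliance separately.

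Have each rater note at every examination whether she knew the regimen, and report that proportion by group. Analyse the separately measured pH (Table 1) alongside the VHI as a less subjective check.

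Any analysis that drops ratings marked as known should be exploratory only. The mark arises after treatment starts and may depend on regimen, so exclusion could introduce a selection of its own.

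The cost is a change in form handling and visit order plus one tick-box, with no extra raters or examinations. Masking will be incomplete where a woman mentions her drug or is known to the rater; where it fails, list this as a limitation. The change protects only ratings made after it takes effect, so it is best made early in recruitment.

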### Statistical analysis

This study utilized both the full analysis set (FAS) and the per-protocol set (PPS) for statistical evaluation. The FAS will include all enrolled participants who receive at least one dose of treatment and provide baseline data, analyzed according to their assigned group to minimize selection bias. The PPS will comprise participants who complete the study per protocol, excluding those with major violations such as non-adherence to treatment or loss to follow-up exceeding predefined thresholds. All tests will be two-sided, with a significance level of *α* = 0.05. Descriptive statistics will summarize continuous variables as mean ± standard deviation for normally distributed data or as median (interquartile range) for skewed distributions. Categorical variables will be presented as frequencies and percentages.

Given the observational nature of this cohort study, baseline imbalances between groups will be assessed using standardized mean differences. If substantial imbalances are detected (standardized mean difference >0.1 for key covariates), propensity score matching will be applied to create balanced subgroups for comparative analyses, with propensity scores estimated via logistic regression incorporating variables such as age, BMI, tumor stage, hormone receptor status, and chemotherapy history.

Between-group comparisons will use independent samples t-tests or Mann–Whitney U tests for continuous variables, depending on data distribution and variance homogeneity. Chi-square or Fisher’s exact tests will be applied for categorical variables.

For longitudinal analyses, we plan to use linear mixed-effects models (LMM) for continuous clinical outcomes (e.g., GSM symptom scores) and generalized linear mixed models (GLMM) for microbiome features (e.g., relative abundance of key taxa). Therapy group, time point, and their interaction will be included as fixed effects to evaluate whether temporal trajectories differ by treatment type. Repeated measures ANOVA (RM-ANOVA) will be retained only as a secondary sensitivity analysis for complete-case datasets. If the proportion of missing data for a given outcome exceeds 10%, multiple imputation by chained equations (MICE) will be performed under the missing-at-random (MAR) assumption, with 20 imputed datasets and pooled estimates using Rubin’s rules.

Multivariable analyses will incorporate multiple linear regression and mixed-effects models, adjusting for confounders such as age, body mass index (BMI), tumor stage, hormone receptor status, and chemotherapy history. Stepwise regression will select variables to evaluate the independent effects of endocrine therapy regimens on vaginal microbiota changes. To address multiple comparisons across primary and secondary outcomes, Bonferroni correction will be applied where appropriate. Pre-specified subgroup analyses will be conducted, stratified by factors such as chemotherapy history and baseline estrogen levels, to explore heterogeneity of effects. Sensitivity analyses will verify result robustness, and subgroup findings will be interpreted cautiously as exploratory. All statistical analyses were executed using SPSS version 26.0 and R version 4.0 software.

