### Patient involvement

The inclusion criteria for the study are as follows: (1) Female participants aged between 18 and 45 years; (2) Histopathological confirmation of invasive breast carcinoma; (3) Positive status for hormone receptors, specifically estrogen receptor (ER) and/or progesterone receptor (PR); (4) Premenopausal status at diagnosis, characterized by baseline follicle-stimulating hormone levels below 40 IU/L and estradiol levels exceeding 20 pg./mL; (5) Scheduled to undergo ovarian function suppression in conjunction with endocrine therapy; (6) Absence of GSM-related symptoms prior to the initiation of treatment; (7) Provision of written informed consent by the participants.

Exclusion criteria included: (1) the presence of concurrent malignancies; (2) severe dysfunction of cardiac, hepatic, or renal systems; (3) pregnancy or lactation; (4) a history of vaginal infection; (5) the use of antibiotics or hormonal medications within the preceding 3 months; (6) an expected survival of less than 2 years [determined by the PREDICT tool^1^ or multidisciplinary team consensus]; (7) patients with psychiatric disorders or those who have been on active treatment with medications known to significantly alter sexual function (e.g., SSRIs, SNRIs); and (8) Patients with active high-risk HPV infections or abnormal cervical cytology requiring intervention.

This study employed a systematic recruitment strategy at Women’s Hospital, Zhejiang University School of Medicine, leveraging its role as a regional center for breast cancer care. Research coordinators reviewed pathology reports daily to identify newly diagnosed patients, conducting preliminary screenings based on age and demographics to compile a list of potential participants. Recruitment was timed post-diagnosis disclosure but pre-treatment planning to enhance receptivity, avoiding the day of diagnosis to reduce emotional burden.

The structured process included: (1) Initial clinician-led introduction during routine visits, with interested patients referred to the research team; (2) Face-to-face detailed explanations of study objectives, procedures, risks, and benefits by coordinators or nurses; (3) A minimum 24-h consideration period without pressure; (4) Signing of informed consent after addressing queries; and (5) Immediate baseline data collection and examinations. This approach aimed to minimize bias and ensure ethical enrollment of 110 participants over 6 months.

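### Baseline GSM symptom VAS is zero by eligibility, yet the mixed model reads as including baseline as a time point; the VAS scores should be modelled at follow-up visits only, with visit-specific covariance

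*Protocol article*

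**What the plan says.** Four statements in the protocol article have to be read together.

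- **Eligibility.** The inclusion criteria (Patient involvement) require "Absence of GSM-related symptoms prior to the initiation of treatment". Secondary outcomes repeats the rule: "only patients who report no GSM symptoms are eligible for inclusion".
- **Scale.** The VAS for dryness, dyspareunia and burning runs from 0 to 10, with "0 indicating no symptoms and 10 indicating the most severe symptoms".
- **Schedule.** The VAS is "completed by patients at each time point from baseline to 12 months". Table 1 lists it at baseline and at months 1, 3, 6 and 12.
- **Model.** Statistical analysis plans "linear mixed-effects models (LMM) for continuous clinical outcomes (e.g., GSM symptom scores" among others, and adds: "Therapy group, time point, and their interaction will be included as fixed effects". It also states that "Repeated measures ANOVA (RM-ANOVA) will be retained only as a secondary sensitivity analysis for complete-case datasets".

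The article names no random-effects or covariance structure, and it does not say whether the baseline record is part of the response.

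**The concern.** If every eligible woman scores 0 at baseline, one of the five visits has no variance and no covariance with any later visit. An ordinary mixed model with a patient effect and one residual variance assumes the same variance at every visit and the same correlation between every pair. It averages over a structure that cannot hold here, and the average sets the standard error of each baseline-to-visit comparison between regimens.

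The interaction is how the article proposes to judge whether symptom trajectories differ by regimen, and the Discussion hypothesises worse GSM symptoms under OFS + AI. A mis-sized standard error bears directly on that secondary comparison. Leaving the covariance free does not help while baseline stays in the response, because an unstructured five-visit matrix with a zero row and column is singular.

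**Working it through.** **The plan's own figures.** The article gives none for this analysis. Its one computed sample size, 25 per group, concerns the Simpson index. It is reproduced with d = 0.8 from the Abstract, 2 × (1.96 + 0.84)² / 0.8² = 24.5, and has no bearing here.

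**Inputs from the document.** Five VAS visits; baseline VAS = 0; 55 per group with 10% attrition, so about 49 per group; two-sided α = 0.05.

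**Assumptions, not in the document.** Within-patient correlation r of the follow-up scores from 0.3 to 0.8. Follow-up SD either constant (2 at each visit) or rising (1, 1.5, 2, 2.5). A random-intercept model with one residual variance. The Introduction says symptoms tend to worsen, which makes a rising SD plausible but gives no size.

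**Formula.** In balanced data this model estimates the residual variance as the mean visit variance minus the mean covariance over the 10 visit pairs. Per patient, it takes the variance of a change from baseline as twice that residual. The true value is the follow-up variance at that visit, because baseline is constant. Type I error is 2 × [1 − Φ(1.96 × SE ratio)], where the SE ratio is model SE over true SE.

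**A. Constant follow-up variance v (effect of baseline alone).** Mean variance = 4v/5 = 0.8v. Mean covariance = 6rv/10 = 0.6rv. Model over true variance = 2(0.8 − 0.6r) = 1.6 − 1.2r, the same at every visit.

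| r | variance ratio | SE ratio | type I error | simulated |
|---|---|---|---|---|
| 0.3 | 1.24 | 1.11 | 2.9% | 2.8% |
| 0.5 | 1.00 | 1.00 | 5.0% | 5.4% |
| 0.7 | 0.76 | 0.87 | 8.8% | 8.9% |
| 0.8 | 0.64 | 0.80 | 11.7% | 11.4% |

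(5,000 null simulations per row, 49 per group, month-12 contrast.)

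**B. Rising SD, month 12.** Variances are 1, 2.25, 4 and 6.25. Mean over five visits = 13.5/5 = 2.7. The six SD products sum to 17.75, so mean covariance = 1.775r. Model variance = 2(2.7 − 1.775r), against a true 6.25. If baseline is dropped but one common variance is kept, model variance = 13.5/4 = 3.375 at any r. The SE ratio is then √(3.375/6.25) = 0.735, and type I error is 15.0%.

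| r | SE ratio, baseline in | type I, baseline in | type I, baseline out, common variance |
|---|---|---|---|
| 0.3 | 0.83 | 10.3% | 15.0% |
| 0.5 | 0.76 | 13.6% | 15.0% |
| 0.7 | 0.68 | 18.1% | 15.0% |
| 0.8 | 0.64 | 21.0% | 15.0% |

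So in this setting baseline moves the error by −4.7, −1.4, +3.1 and +6.0 percentage points around 15.0%. At month 1 the model SE is 2.08 to 1.60 times the true one as r goes from 0.3 to 0.8, so power there is reduced. Here too unequal variance is the main cause: without baseline the ratio is √(3.375/1) = 1.84.

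**C. Omnibus interaction test.** Over both SD patterns, simulated type I error is 5.5% to 8.8% with baseline in, and 4.6% to 6.8% on follow-up visits only.

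**D. After the fix.** With visit-specific variances or an unstructured matrix on the four follow-up visits, the SE ratio is 1.00 and type I error 5% in both patterns.

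**The case against.** The strongest reply is that the article does not specify the faulty model. It states no random intercept and no single residual variance, and does not literally put baseline in the response. A journal article may leave such choices to an analysis plan that is not shown. This stands in part: the sizes above are conditional on a default model. What remains is that the article fixes eligibility, scale, schedule and fixed effects, calls baseline a time point, and then models time point. The natural reading is a five-visit response, and on that reading an unstructured covariance cannot be fitted.

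Other choices could soften the fault. Robust standard errors would largely repair the contrasts, but Statistical analysis does not name them; generalized estimating equations appear only in the Abstract and Discussion. In a very small check (12 runs per setting), a random slope brought the mean model SE closer to the truth in three of four settings and further away in one (0.477 against a true 0.404). The planned repeated-measures ANOVA rests on a common variance of differences, so it offers no independent check.

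Exact zeros are also an inference. Eligibility is screened by questionnaires that are not named, with no VAS cut-off.

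A reader might infer that the constant baseline itself produces the 10–21% errors at month 12. The working does not support that: with the same rising SDs and baseline removed, a common-variance model still gives 15.0%. Nor can one conclude that standard errors are always too small, or too narrow late and too wide early. With constant follow-up variance the error is the same at every visit, and its sign changes at r = 0.5.

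**Conclusion.** The point holds as a conditional one, of moderate weight. On the natural reading, the VAS response contains one visit that eligibility makes constant, provided that absence of symptoms is recorded as 0. Under a default random-intercept model, baseline alone shifts the standard error by about +11% to −20% for correlations of 0.3 to 0.8. Type I error is then about 3% at 0.3, nominal at 0.5, and 9–12% at 0.7–0.8. The omnibus interaction test is inflated only mildly. If follow-up variance rises as assumed, single-visit errors at month 12 reach about 10–21%, chiefly because follow-up variances are unequal. Correlations and SDs are assumptions throughout.

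The reach is limited to the three VAS items, which are secondary. A reader might extend it to the primary outcomes, but eligibility does not fix the microbiome measures or the VHI, and they are unaffected. Whether the ICIQ-SF is fixed at baseline depends on whether urinary symptoms counted in the GSM screen, which the article does not settle.

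**What to change.** State that the VAS scores for dryness, dyspareunia and burning are modelled at months 1, 3, 6 and 12 only, with regimen, visit and regimen × visit as fixed effects, an unstructured or visit-specific covariance, and robust standard errors. Dropping baseline alone is not enough if variances rise.

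Say also how the contrasts are then read. Each follow-up score already is the change from zero, so the regimen difference at a visit replaces the old baseline-to-visit interaction contrast. The overall test of differing trajectories becomes the joint test of regimen and regimen × visit; the interaction term alone would miss a difference that is constant from month 1 on.

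State whether absence of symptoms means VAS = 0. If some non-zero baseline scores are admitted, use baseline as a covariate. For the VHI and any other score not fixed by eligibility, keep the baseline information.

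The cost is a sentence or two of model specification. No new data are needed, and no information is lost, because a constant record carries none.
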